## Abstract

**Introduction:**

Suspected urinary tract infection (UTI) ranks among the most common reasons for antibiotic use in nursing homes. However, diagnosing UTI in this setting is challenging because UTI often presents with non-specific symptomatology. Moreover asymptomatic bacteriuria is common in elderly, which complicates attribution of causality to detection of bacteria in urine. These diagnostic challenges contribute to overuse of antibiotics and emergence of antimicrobial resistance in nursing homes. Given the diagnostic challenges, there is a need for point-of-care (POC) diagnostic tests to support clinical rules for diagnosing UTI. Procalcitonin (PCT) and C reactive protein (CRP) are inflammatory blood markers that have been proven useful to support diagnosis and monitoring of (bacterial) respiratory tract infections and sepsis. While limited studies suggest their usefulness in supporting UTI diagnosis, their utility has not been studied in elderly populations for this purpose.

**Methods and analysis:**

In a 24-month matched prospective study, ‘PROGRESS’ will assess and compare the sensitivity of rapid POC measurements of blood CRP and PCT levels to support clinical rules for diagnosing UTI in nursing home residents. The primary outcome measure is sensitivity of the POC tests to identify patients with true UTI based on the predefined definition, as derived from receiver operating curves.

**Ethics and dissemination:**

This study will be conducted in accordance with Good Clinical Practice guidelines and the principles of the Declaration of Helsinki. The study protocol is approved by the Medical Ethical Committee of Amsterdam UMC location VUmc with reference number 2017.350 and National Central Committee on Research involving Human Subjects with reference number NL62067.029.17.

**Trial registration number:**

NTR6467.

Strengths and limitations of this studyStringent post hoc urinary tract infection criteria incorporating microbiology result and clinical response to adequate antibiotic therapy.Sensitivity in relevant study population, namely nursing home residents.No on-site point-of-care test (POCT), however, POCT is performed within 4 hours.Single country study.

## Introduction

Antimicrobial resistance (AMR) is mainly driven by the inappropriate antibiotic use in both humans and animals. AMR is a problem in worldwide. Nursing homes are increasingly regarded as an important reservoir for the emergence of AMR.^1–4^

The most frequently reported infections in elderly residents are urinary tract infections (UTIs).^5^ In Dutch nursing homes, an average weekly incidence of 10.3 (95% CI 9.8 to 10.8) per 1000 elderly residents was found.^6^ UTI is the most common reason for prescribing antibiotics in Dutch nursing homes. However, not all diagnosed UTIs are ‘true’ UTIs since recognition and diagnosing UTI in nursing homes is complex. Approximately one-third of elderly residents UTIs are misdiagnosed, leading to inappropriate antibiotic use.^7 8^ This is mainly due to the facts that non-specific, non-urinary tract symptoms, such as altered mental status, are often attributed to UTIs while asymptomatic bacteriuria (ASB), possibly resulting in positive urine tests, is also common in the elderly residents.^9^

### Cognitive impairments and UTIs

The majority of nursing homes in the Netherlands consist of psychogeriatric wards (57%), for elderly residents suffering from cognitive impairments, mainly Alzheimer disease.^10–13^ Their ability to verbally communicate or express classical symptoms of UTI, such as dysuria, urgency or frequency, is often limited.^14^ The most frequently presented symptom in elderly residents leading to antibiotic prescription for a suspected UTI is an altered mental status (43.3%), while classical symptoms as dysuria, urgency and frequency are present in the minority of cases (0%–3.8%).^15^ Confusion or an altered mental state is a non-specific symptom and can result from other infectious and non-infectious diseases in the elderly residents.

### Asymptomatic bacteriuria

ASB is defined by the presence of significant bacteriuria without symptoms of UTI. ASB is thus regarded as colonisation of the urinary tract rather than infection. ASB is highly prevalent in healthy elderly persons with reported prevalence rates as high as 40%–50%.^16 17^ In the presence of ASB, frequently used urine tests based on detection of bacteria are less applicable to diagnose UTI, because detection of bacteria does not discriminate between ASB and UTI. In combination with above described non-specific symptomatology, it is difficult to distinguish ASB from ‘true’ UTI in the elderly.

### C reactive protein and procalcitonin

In the diagnosis of respiratory tract infections and monitoring of bacterial sepsis, inflammatory markers, such as C reactive protein (CRP) and procalcitonin (PCT) in blood, have proven useful to guide antibiotic therapy and reduce antibiotic use.^18–21^ Currently, point-of-care (POC) CRP measurements are recommended by Dutch guidelines for the general practitioners to guide antibiotic treatment for acute respiratory tract infections. CRP and PCT represent potential candidates for rapid POC testing (POCT) to support UTI diagnosis.

Ageing and frailty are associated with changes in serum inflammation protein levels, such as CRP and PCT.^22–24^ Therefore, it is important to determine cut-off values for CRP and PCT specifically in the elderly nursing home resident population.

### Inflammatory markers CRP and PCT in UTI

Studies in adults showed that CRP and PCT levels in parenchymatous infections (acute pyelonephritis, prostatitis and epididymitis) are increased.^25 26^ Using a PCT-based algorithm in UTI treatment was shown to reduce antibiotic exposure in adults.^27^ In a subgroup analysis including elderly (>70 years of age) with lower UTI antibiotic exposure was reduced as well, suggesting a potential role for PCT.

In children with UTI, sensitivity of CRP (cut-off 20 mg/L) and PCT (cut-off 0.5 ng/mL) in predicting pyelonephritis is high (94% and 86%, respectively), but specificity varies (39% and 74%, respectively)).^28^ However, the number of studies in this systematic review was limited and the heterogeneity substantial. The specificity and positive predictive values varied because CRP and PCT were also increased in children with lower UTI. This suggests a possible role for inflammatory markers in distinguishing UTI (upper and lower UTI) from no inflammation (ASB), where studies are lacking.

In the elderly population, only three studies have been performed evaluating CRP and PCT and their possible role in UTI.^29–31^ These studies focused on hospitalised and more severely ill elderly populations, making the results not applicable to the nursing home population. In 13% of the healthy elderly controls, CRP values were increased,^30^ again suggesting increased inflammation in ageing and frailty, indicating the need to determine specific cut-offs in elderly. Studies on lower UTIs and CRP or PCT in elderly are scarce.

### Distinguishing UTI and ASB

The majority of UTIs in elderly residents are lower UTIs without fever or other signs of systemic illness,^32 33^ while most studies on CRP and PCT in UTI focus on diagnostic values in upper UTI or focus on distinguishing upper and lower UTI. The only small study on distinguishing lower UTI (infection) from ASB (colonisation) in adults, shows a high negative predictive value for UTI of PCT levels at a cut-off of 0.25 ng/mL^34^, suggesting that low PCT levels can rule out UTI and contribute to reducing antibiotic use.

In conclusion, decisions about who to treat and who not to treat are challenging in elderly residents with suspected UTI, resulting in potential antibiotic overuse in those who do not need treatment. Availability of a simple and rapid POC test to distinguish true UTI from ASB represents an unmet need that would greatly assist clinical management of these vulnerable patients, by improving appropriateness of antibiotic treatment and by enabling consideration of alternative causes of presenting non-specific symptomatology when UTI is unlikely.

## Methods and analysis

### Aim

To assess the sensitivity of POC measurements of blood CRP and PCT levels to support clinical rules for diagnosing UTIs in elderly nursing home residents.

### Outcome

The primary outcome is the sensitivity of the POC test to identify patients with a true UTI based on the predefined definition, as derived from receiver operating curves (ROC).

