### Sample size

For the sample size calculation, we used a two-sided p value of 0.05 and a power of 90%. We assume a difference in sensitivity between the two POCTs of at least 10% as clinically relevant. This difference is the net result of discordant test outcomes between the two tests. The magnitude of discordance is the main parameter in the McNemar test used to calculate the sample size for the matched design.

With a proposed sample size of 440 enrolled participants, we are able to adequately assess an increased sensitivity of 10% or more, when the prevalence of UTI in the study population is 40% or more. If the prevalence if UTI is lower, the difference in prevalence that is statistically significant (at the 5%) level increases to 11% or 12%.

Based on data of the national sentinel surveillance network for infectious diseases in nursing homes (SNIV) in 2015, the prevalence of UTI in Dutch nursing homes is 10.3 in 1000 patient weeks. UTI definition by SNIV is broader where response to adequate antibiotic treatment is not taken into account.

In order to reach the target, the PROGRESS study will take place in 13 nursing homes with around 1350 elderly residents in total. Recruitment of a manageable number of approximately 12 participants per week in total is anticipated.

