### Data and statistical analysis

The sensitivity of both POCTs to diagnose UTIs defined by the post hoc definition is derived from the optimal point of an ROC. Sensitivities of CRP and PCT tests are compared by a matched analysis approach using a two-tailed McNemar test assessing the statistical significance of differences between the sensitivities of each pair of tests (performed in each study participant).

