## Discussion

This trial will test the hypothesis that increased levels of inflammatory markers support the diagnosis of UTI in elderly and can guide empirical antibiotic treatment in nursing homes. Although our study involves the target population (elderly nursing home residents), found CRP and/or PCT cut-off values need to be confirmed by prospective trials. Besides test sensitivity, the potential impact on antibiotic prescription needs to be established in a consecutive, randomised controlled, study.^41^ The aim of this study is assessing the sensitivity of POCT CRP and PCT in current clinical practice. This clinical setting is suboptimal for urine collection, where urine incontinence complicates collection methods. Chamber pots and diapers are frequently used, which introduce the risk of UTI overestimation by positive dipstick urinalysis and bacterial cultures. Although we have shown in our add-on laboratory study that diapers can be used for UTI diagnosis, the outcome can be affected by suboptimal urine collection.

In this population, a reference test for UTIs does not exist, this is the actual gap we are trying to address. To reduce classification bias when a reference test is lacking, we use a post hoc definition of ‘true’ UTI.^42^ We defined a stringent definition of UTI that in our opinion makes a clear distinction between UTI and ASB. We will perform post hoc analysis in which UTI definition is less stringent to assess the effects of potential misclassification of the outcome. UTI definition in this post hoc analysis will include classical UTI symptoms irrespective of resolution with adequate antibiotics, in accordance with the Dutch national guidelines.^43^ We will include this procedure in the current amendment and data analysis plan that is drawn up before the completion of the data collection.

Since effectiveness of a new test does not just depend on its proven efficacy in research studies, but also on successful implementation after the study, qualitative research on identifying the barriers and facilitators for implementation are needed and will be performed in parallel to the described study.

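### The primary sensitivities are read at cut-offs chosen in the same participants, and the McNemar comparison treats those cut-offs as fixed

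*Protocol article*

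**What the plan says.** The Outcome section states that "The primary outcome is the sensitivity of the POC test to identify patients with a true UTI based on the predefined definition", read from ROC curves. Data and statistical analysis adds that the sensitivity of each test "is derived from the optimal point of an ROC". It then compares the two sensitivities "using a two-tailed McNemar test assessing the statistical significance of differences between the sensitivities of each pair of tests".

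No threshold for CRP or PCT is set beforehand. The background on the two markers gives the reason: "it is important to determine cut-off values for CRP and PCT specifically in the elderly nursing home resident population". The criterion that makes a point optimal is not named. The article describes no split sample, cross-validation or bootstrap.

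The Discussion gives the one caveat: "found CRP and/or PCT cut-off values need to be confirmed by prospective trials".

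**The concern.** A threshold picked because it performs best in a data set looks better there than it will elsewhere. The sensitivity reported at it is a resubstitution value, and resubstitution values are biased upward.

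The test has a second problem. McNemar's statistic counts discordant pairs among UTI cases and allows only for binomial noise in those counts. It does not allow for movement of the two cut-offs from sample to sample. When each cut-off slides along its own ROC curve, sensitivity is traded against specificity, and two equally good tests can show different sensitivities only because their cut-offs landed at different places. What is at stake is the primary estimate and the one significance test the protocol fixes for it.

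**Working it through.** **The plan's own figure.** The Sample size section states that "we used a two-sided p value of 0.05 and a power of 90" per cent, with a 10-point difference, 440 participants and a UTI prevalence of 40%.
- Cases: 440 × 0.40 = 176. Non-cases: 440 − 176 = 264.
- Paired formula: cases = (1.96·√p + 1.2816·√(p − d²))² / d², with d = 0.10 and p the discordant proportion.
- The article gives no value for p. At p = 0.17: (1.96 × 0.4123 + 1.2816 × 0.4000)² / 0.01 = 174.4, and 174.4 / 0.40 = 436, close to 440.
- With the design effect of 1.1 listed under Protocol version, 440 / 1.1 = 400 participants and 160 cases, which corresponds to p of about 0.156.

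So 440 is attainable. The calculation assumes fixed cut-offs.

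**Assumptions not in the documents.** Equal-variance binormal markers, AUC 0.65–0.90, and a CRP–PCT correlation of 0.5 for the comparison. Two common criteria were tried: the Youden index and the point closest to the (0,1) corner. With separation μ = √2·Φ⁻¹(AUC), both have the same population optimum, with sensitivity Φ(μ/2). At AUC 0.80: μ = 1.190 and sensitivity = Φ(0.595) = 0.724.

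**Simulation, 176 cases and 264 non-cases, 4,000 replicates.** Coverage is of a nominal 95% Wilson interval that takes the cut-off as fixed.

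| | Youden, AUC 0.70 | 0.80 | 0.90 | Closest, AUC 0.70 | 0.80 | 0.90 |
|---|---|---|---|---|---|---|
| Mean apparent sensitivity | 0.66 | 0.738 | 0.828 | 0.657 | 0.736 | 0.827 |
| Mean true sensitivity at chosen cut-off | 0.635 | 0.717 | 0.810 | 0.639 | 0.720 | 0.813 |
| Excess, points | 2.5 | 2.1 | 1.8 | 1.8 | 1.6 | 1.4 |
| SD of apparent sensitivity | 0.097 | 0.071 | 0.048 | 0.048 | 0.040 | 0.031 |
| Fixed-cut-off SE | 0.035 | 0.033 | 0.028 | 0.036 | 0.033 | 0.028 |
| Coverage of sensitivity at population optimum | 50% | 64% | 73% | 82% | 90% | 92% |
| McNemar rejection, equal markers | 55% | 43% | 31% | 20% | 16% | 9% |

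With fixed cut-offs the same McNemar test rejects 4.5–6% of the time.

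Over the whole AUC range 0.65–0.90 the results are:
- excess 1.8–2.7 points (Youden) and 1.4–1.8 (closest);
- coverage of the population-optimal sensitivity 45–77% and 82–95%;
- coverage of the true sensitivity at the cut-off actually selected 91–95% under either rule;
- McNemar rejection 32–62% and 8–23%.

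Separate runs and interval types (Wilson, Clopper–Pearson) differ by a few points at most.

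**Check of the McNemar result by hand, AUC 0.80, correlation 0.5.** Under equality McNemar assumes the difference in sensitivities has SE √(discordance / cases).
- Youden: mean discordance 0.272, so √(0.272/176) = 0.0393. The simulated SD of the difference is 0.096, a ratio of 2.44. Rejection ≈ 2·[1 − Φ(1.96/2.44)] = 2·[1 − Φ(0.803)] = 0.42, against 0.43 simulated.
- Closest: √(0.269/176) = 0.0391, SD 0.054, ratio 1.38. Rejection ≈ 2·[1 − Φ(1.42)] = 0.16, as simulated.

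**Fewer cases.** At an assumed prevalence of 15% (440 × 0.15 = 66 cases) and AUC 0.6–0.9, the excess is 3.8–6.0 points (Youden) or 2.8–3.9 (closest).

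**The case against.** The strongest reply is that the study derives cut-offs and says so. The Discussion asks for confirmation in later prospective trials. The optimism of 1.4–2.7 points is smaller than one binomial standard error at AUC 0.65–0.80 (3.3–3.7 points) and well below the 10-point difference taken as clinically relevant. This stands as to size. It does not remove the point, because later confirmation of a cut-off leaves this study's own sensitivity and test uncorrected.

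A reader might infer that the reported precision will be badly overstated. The documents do not support that. They specify no confidence interval for sensitivity, and a separate analysis plan may do so. Low coverage arises only if the target is the sensitivity at the population-optimal cut-off, and it is severe only under Youden. For the true sensitivity at the cut-off actually selected, a fixed-cut-off interval does nearly what it claims (91–95%). Nor does any section say that a randomised study would be planned on this sensitivity figure. The Discussion says only that such a study is needed.

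It can also be said that McNemar is right for the two cut-offs as selected, since their true sensitivities do differ. That is so. But the difference then reflects where each cut-off fell, at the expense of specificity, and not which marker detects UTI better. The comparison is presented as one between the tests.

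**Conclusion.** The point holds. The article itself fixes the estimate at a data-chosen optimum and fixes McNemar as the comparison, so this is a stated method and not a detail left to another document. The bias in each sensitivity is modest: about 1.4–2.7 points at 176 cases, and more if there are fewer cases. The larger fault is in the comparison, where false rejection is about 32–62% under Youden or 8–23% under closest-to-corner, against a nominal 5%. Understated interval width is a conditional risk only.

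The sizes rest on the binormal model, AUC 0.65–0.90 and a correlation of 0.5, none of which the documents give, and on which criterion is used. The direction was the same under both criteria and at every AUC tried.

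**What to change.** In Data and statistical analysis:
- Name the criterion that defines the optimal point.
- Make the primary estimate the optimism-corrected sensitivity, reported with its paired specificity. Obtain it from a bootstrap that resamples participants, so that the CRP–PCT pairing is kept, and re-selects both cut-offs in every resample. Give intervals for sensitivity, specificity and cut-off.
- Base the CRP-versus-PCT comparison on the same bootstrap. Alternatively, compare sensitivities at a specificity fixed in advance, with the uncertainty of the threshold carried through.
- Show the apparent values as secondary.

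This needs no new data or participants, only a change of wording and a short program. The price is slightly lower sensitivities, wider intervals, and less power for the 10-point difference than the stated McNemar calculation implies.

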### Design and setting

In a prospective matched study, we will assess and compare the sensitivity of rapid POC measurements of blood CRP and PCT levels to support clinical rules for diagnosing UTI in elderly residents, with a post hoc definition of UTI with stringent criteria including microbiology results as gold standard. The start date of this study is November 2017 and the planned end date is December 2019.

In this study, a true UTI is present when the following five criteria are met: presence of at least two urinary or non-specific symptoms (1) positive urine leucocyte esterase test (2) presence of uropathogens in bacterial culture at 10^4^≥ colony forming units (CFU)/mL (3) maximum of two uropathogens present (4) and symptom resolution in the course of adequate antibiotic treatment, where adequate treatment is defined by proven susceptibility of isolated uropathogens to the administered antibiotic (5).

The matching refers to the assessment of blood CRP and PCT levels in the same study participants. The study will be performed in nursing homes of the University Network for Organizations of Elderly Care of the VUmc University Medical Center. The expected study duration is 24 months.

The nursing home population in this study consists mostly of psychogeriatric and somatic (long-stay) wards and some rehabilitation (short-stay) wards.

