### Inclusion and exclusion criteria

Eligible for study participation is elderly nursing home residents clinically suspected of UTI by the attending physician or nurse. Exclusion criteria are suspected respiratory tract infection, suspected other infection requiring antibiotic therapy, previous study inclusion in the past 30 days or lack of written informed consent.

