#### Data on signs and symptoms, clinical response and antibiotic use

The attending physician or nurse collects demographic data and data on signs and symptoms of UTI at the day of study enrolment (day 0), see figure 1. The attending physician or nurse will evaluate improvement of signs and symptoms at day 5 and 10 and hospitalisation and/or mortality at day 10. The research physician will visit the nursing homes regularly for monitoring of follow-up. Data on antibiotic use (timing of initial antimicrobial therapy, type of antimicrobial agent and possible switch in antimicrobial therapy) will be collected by the research physician 10 days after study enrolment.

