#### Urine sample collection, dipstick analysis and bacterial culture

**Figure 1 F1:**
[figure not shown]
Data collection progress study. *Participants and attending physicians/nurses will not be informed of results (blinded). CRP, C reactive protein; PCT, procalcitonin; POCT, point-of-care testing.

The attending nurse will collect an urine sample for purpose of this study. Urine samples are collected spontaneously voiding either directly in a sterile urine container or in chamber pot (insert pan). When participants have an indwelling urine catheter, urine will be collected when the urine bag is changed. When participants suffer from urinary incontinence or are not able to urinate on the toilet or chamber pot, diapers will be used to obtain urine for bacterial culture and dipstick analysis^36 37^ Urine extraction from diapers can provide a reliable diagnostic specimen, if faecal contamination can reasonably excluded.^38^ Date, time and way of urine collection method are registered by the attending nurse. The urine sample is stored at 4°C.

For dipstick analysis Combur 2 (Roche Diagnostics) will be used (nitrite and leucocyte esterase) by the research physician. Urine will be used for semiquantitative bacterial culture. Inoculation of 10 µL urine to CHROMID CPS Elite (Chromogenic Medium for the immediate identification of *E. coli*, *Proteeae* and *Enterococcus*) agar (Biomerieux) and Columbia Colistin Nalidixin Acid (CNA) agar with 5% sheep blood (Biomerieux) will be streaked using a four quadrant pattern. Bacterial growth will be interpreted after overnight incubation at 35°C in aerobic (CPSE) and CO_2_ enriched (CNA) environment. Uropathogens will be identified by Maldi-tof mass spectrometry (Microflex, Bruker Daltonic). All primary and secondary uropathogens in the European Consensus Guideline are considered as uropathogens in this study. Doubtful isolates are considered as non-uropathogens.^39^ When bacterial growth of ≥10^4^ CFU/mL is found, antibiotic susceptibility testing will be performed using the VITEK2 platform (BioMérieux). Unlike the European Consensus Guideline, for all uropathogens ≥10^4^ CFU/mL growth will be used as cut-off, as urine collection methods will differ and the presence or absence of specific urinary symptoms. Participants, attending physicians and nurses will not be informed of urine dipstick and bacterial culture results (blinded).

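### Criterion 5 counts symptomatic, culture-positive residents as non-UTI when their response to an active antibiotic could not be observed, which contaminates the ROC comparator

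*Protocol article*

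**What the plan says.** The article's Design and setting section states that "a true UTI is present when the following five criteria are met". The first four criteria are at least two symptoms (urinary or non-specific), a positive leucocyte esterase test, uropathogen growth at the stated threshold, and no more than two uropathogens. The fifth is "symptom resolution in the course of adequate antibiotic treatment, where adequate treatment is defined by proven susceptibility of isolated uropathogens", meaning susceptibility to the drug that the resident received. No third category is described.

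Four other places bear on how the rule works:

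- **Entry** (Inclusion and exclusion criteria) requires that the resident be "clinically suspected of UTI by the attending physician or nurse". Antibiotic treatment is not a condition of entry.
- **Blinding** (Urine sample collection, dipstick analysis and bacterial culture): the treating staff do not see the study's dipstick or culture results.
- **Follow-up** (Data on signs and symptoms, clinical response and antibiotic use): the treating staff "will evaluate improvement of signs and symptoms at day 5 and 10 and hospitalisation and/or mortality at day 10".
- **Analysis**: the section on data and statistical analysis opens by applying the definition directly: "The sensitivity of both POCTs to diagnose UTIs defined by the post hoc definition is derived from the optimal point of an ROC".

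The Discussion acknowledges possible misclassification of the outcome. It plans a further analysis that uses classical UTI symptoms and ignores response to treatment.

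**The concern.** Criterion 5 combines two things: whether infection was present, and whether the resident happened to receive an active drug and was observed until symptoms resolved. A resident who meets criteria 1 to 4 and whose symptoms persist on an active drug fails on evidence. A resident who had no antibiotic, had one to which the isolate is not susceptible, or died before resolution fails without any evidence against infection. Because entry needs only suspicion, and the study culture cannot inform the choice of drug, such residents can occur.

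Under an all-or-nothing rule they join the group against which CRP and PCT are judged. Infected residents in that group make both markers look less able to discriminate. Cut-offs matter here too: the article says cut-offs specific to this population are needed, and the Discussion expects those found to go forward to confirmatory trials.

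**Working it through.** **1. Who fails, and why.** Among residents meeting criteria 1 to 4:

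| Course | Criterion 5 by the literal rule | Evidence against UTI? |
|---|---|---|
| Active drug, symptoms resolve | met | – |
| Active drug, symptoms persist | not met | yes, on the plan's own logic |
| No antibiotic | not met | no |
| Isolate not susceptible to the drug | not met | no |
| Death before resolution | not met | no |
| Hospitalised, response not observed | not met | no |
| Hospitalised, resolution on an active drug observed | met | – |

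**2. Contamination of the comparator.** Let π be the true UTI prevalence among those enrolled and f the share of true UTIs that fail criterion 5 only because it is not assessable. The documents do not give f; 10–40% is assumed. For π, 40% is the planning figure in the Sample size section and 50% is an assumption. The UTI share of the comparator is m = πf / (πf + 1 − π).

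With 440 enrolled and π = 40%, there are 176 infected and 264 not infected. At f = 10%, 17.6 infected residents are misfiled and m = 17.6/281.6 = 6%. At f = 40%, 70.4 are misfiled and m = 70.4/334.4 = 21%.

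**3. Effect on AUC and specificity if the misfiled UTIs have average marker levels.** Assume a true AUC of 0.75.

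- Observed AUC = (1 − m) × 0.75 + m × 0.5.
- Observed specificity = (1 − m) × spec + m × (1 − sens). In an equal-variance binormal model with AUC 0.75, sens = spec = 0.683 at the optimal cut-off.

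| π | f | m | AUC | Specificity |
|---|---|---|---|---|
| 40% | 10% | 0.063 | 0.734 | 0.66 |
| 40% | 40% | 0.211 | 0.697 | 0.61 |
| 50% | 10% | 0.091 | 0.727 | 0.65 |
| 50% | 40% | 0.286 | 0.679 | 0.58 |

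**4. Effect on the primary sensitivity.** The observed Youden index is sens + (1 − m) × spec + m × (1 − sens) − 1 = (1 − m)(sens + spec − 1). This is a constant multiple of the true index. With average-marker contamination, the Youden cut-off and the sensitivity there do not move.

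They do move in two situations:

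- *Failure related to marker level.* Take π = 40%, a separation of 1.0 SD (AUC 0.760), and misfiled cases 0.5 SD higher than other UTIs. As f goes from 0 to 40%, the Youden cut-off falls from 0.500 to 0.413 SD. Observed sensitivity rises from 0.691 to 0.721, and specificity falls from 0.691 to 0.550. With a separation of 1.5 SD and f = 20%, sensitivity goes from 0.773 to 0.784.
- *Another optimality rule.* The article does not say which point is optimal. With the point closest to the upper left corner, AUC 0.75, π = 50% and average-marker contamination of 9–29%, sensitivity falls from 0.683 to 0.671–0.644 and the cut-off rises.

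**5. The planned alternative definition.** It drops response to treatment but also moves to classical symptoms. The section on cognitive impairments and UTIs puts dysuria, urgency and frequency at 0–3.8% of suspected cases treated with antibiotics. Residents with positive cultures and only non-specific symptoms would mostly not be recovered, and two changes at once cannot show what criterion 5 contributes.

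**The case against.** The strongest reply is that the primary outcome is sensitivity at the ROC optimum, compared by McNemar test among UTI-positive residents, whereas the calculable harm falls on AUC and specificity. That stands. A reader might infer that the primary outcome is biased. The documents do not show that failing criterion 5 is related to marker level, and without such a link the Youden cut-off and sensitivity are unaffected. The link is plausible for fatal cases, but under the assumed 0.5 SD shift sensitivity moves by 1 to 3 points, against the 10-point difference that the plan treats as relevant.

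A reader might also take every misfiled resident to be a UTI. The article reports asymptomatic bacteriuria in as many as 40–50% of elderly persons and misdiagnosis in about one-third of residents' UTIs, and criterion 5 is there to separate the two conditions. Some untreated residents meeting criteria 1 to 4 belong in the comparator. Nor does hospitalisation by itself fail criterion 5.

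A loss of power might be inferred as well. The 440 fits a McNemar calculation with 176 UTI-positive residents and discordance of about 0.172, a value the article does not state. On that basis power would fall from 90% to about 87–71% for f = 10–40%, but only if the 40% prevalence is counted before criterion 5 is applied. The article does not say so, and it already allows for lower prevalence.

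Finally, an analysis plan that is not shown may handle these residents, and the Discussion plans a looser definition. This lowers confidence that they will in fact be analysed as non-UTI. It does not answer the point, because the published rule is complete as worded and feeds directly into the ROC, and the looser definition is only partial mitigation.

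**Conclusion.** The concern holds as a flaw in the stated reference standard: residents for whom criterion 5 cannot be assessed are, by the literal rule, counted as negative. With 10–40% of true UTIs affected, 6–21% of the comparator would be UTI at 40% true prevalence and 9–29% at 50%. A true AUC of 0.75 would be seen as about 0.73–0.70 and 0.73–0.68, and specificity would fall by about 2 to 10 points. These sizes rest on the assumed share, true prevalence, AUC and binormal model; none of the four is fixed by the documents beyond the 40% planning figure. Bias in the primary sensitivity and in the cut-off is conditional: it needs failure to be related to marker level, or an optimal point other than Youden's. Severity: should be fixed.

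**What to change.** Add a class to the definition for criterion 5 not assessable: criteria 1 to 4 met, and no antibiotic given, isolate not susceptible to the drug given, or response not observed because of death or hospitalisation. Report its size and its CRP and PCT levels. Prespecify the ROC and McNemar analyses three ways, keeping criteria 1 to 4 unchanged: the class counted as UTI, counted as non-UTI, and excluded. Draw conclusions on sensitivity, specificity and cut-offs only where they hold across all three. State which ROC point is meant by optimal.

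The cost is wording and a little more analysis. Antibiotic use, susceptibility, clinical response, hospitalisation and death are already collected, and no treatment changes. The excluded version should not stand alone: it leaves the UTI-positive group as it is now, and it may narrow the comparator by removing residents with asymptomatic bacteriuria, which could flatter specificity.
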